#### Tailored Package group -- treatment phase

The *Tailored package *is modelled in part on our successful HEAT study [43] and from the literature [2,39,66,69] and is designed to be suitable for incorporation into primary care. Three main areas of interest will be assessed and targeted; dietary intake, physical activity/inactivity, and parenting/behaviour (Table 1). In the *Tailored Package *condition, parents will attend one session with a multi-disciplinary team (consultant session) then all further contact will be with their MInT mentor.

**Table 1 T1:** Goals and target behaviours of interest.

Diet	Behaviour management
Making water the main drink	Stress management for parents
Eating more fruit and vegetables	Using attention and effective commands
Changing fast food choices	Using ground rules and rewards
Healthy snacks	Discipline and consequences
Appropriate portion size	Developing action plans
Family meals	

**Physical activity/inactivity**	**Other**
Motivating kids to be active	Helping children sleep
Reducing screen time	
Increasing moderate/vigorous activity	
Increasing family activity	

#### Consultant session

Information obtained from the screening, follow-up and baseline assessments (family structure, economic situation, dietary intake, physical activity, child behaviour, motivation, parental weight, parenting) will be used by the clinical psychologist to develop a formulation that is specific for each family. This formulation will provide an explanation of factors that may have contributed to the development of the child's weight, and may be maintaining the situation, as well as identifying strengths and resources in the family. The family will then meet with the "expert" team, consisting of the clinical psychologist, a dietitian, an exercise specialist and the MInT mentor to discuss and modify the formulation as appropriate and to reflect on the implications of this for possible goals for change. The main objective of this session is to assist the family in developing an understanding of their current situation, and to collaboratively identify areas in which they may wish to make changes in. Once the goals have been identified, the session will focus on developing an individualised plan for each family consisting of strategies that they can use to achieve the goals they have identified.

#### Mentor sessions - timing

The MInT mentor will then become the main contact for each family. To aid in establishing new routines during the first phase of the treatment period (4 months) the mentor will contact the family each week, using an alternating but flexible schedule of in-person consultations and telephone calls. Frequency of contact will be gradually reduced over the subsequent 20 months of the intervention (fortnightly for months 5-8, monthly for months 9-12, and 3-monthly for months 13-24).

#### Mentor sessions - structure

During the sessions the mentor will assess progress with each goal since last contact, problem-solve with the family any difficulties arising, and negotiate goals for the next session. Each family will receive a different package of resources over time depending on identified need and there is some scope for resources to be tailored to individual families. Across the period of intervention the mentor may also (in consultation with the expert team) facilitate the introduction of new behavioural goals. The intervention will be conducted in the "spirit" of MI, taking a client-centred collaborative approach, which has been identified as just as important as the specific techniques [21], by adhering to the four general principles of expressing empathy, supporting self efficacy, rolling with resistance and developing discrepancy. MI will be used as required through the life of the intervention, in consultation with the supervisors, when motivation and/or engagement is waning, and when at the transition from one target behaviour to the next (where multiple goals have been identified).

#### Training in MI and assessment

##### Training

Researchers providing the MI completed training in MI over 3 months. Training consisted of a general orientation to the history and development of MI, its use and efficacy through reading key resources, and completion of an online training course in the use of MI in healthcare settings run by the Pacific Centre for Motivation for Change (PCMC, http://www.pacificcmc.com/). Researchers also viewed the BMI^2 ^DVD training system (Resnicow, 2009), which introduces MI and provides specific examples of MI for paediatric obesity in medical settings. Researchers completed a 2-day workshop led by a trainer accredited by the Motivational Interviewing Network of Trainers to further develop skills tailored to providing assessment results using MI for paediatric obesity. Skills were maintained through regular individual and group exercises including role-plays, self-review, and analysis of the content of sessions using the Motivational Interviewing Treatment Integrity (MITI) [70] coding schedule (see below) by the MI supervisors.

##### Supervision

Researchers providing assessment results to participants will attend weekly supervision. Supervisors are clinical psychologists who have completed the training received by the researchers. In addition, supervisors have completed training specific to providing supervision, and completed a day with the MI expert trainer (PCMC), focused on coding MI using the MITI coding system and supervision of MI. The MITI will be used in supervision to provide structured feedback about improving practice, in addition to providing quantitative data about the quality of the MI sessions. Prior to supervision, researchers will review a recording and complete a self-reflection exercise involving an analysis of their adherence to MI, strengths and weaknesses and skills. This exercise has been adapted from MI assessment supervisory tools for enhancing proficiency [71]. During supervision, researchers' self-reflections will be reviewed and specific feedback from the MITI will be provided. Collaboratively, the researcher and supervisor will set specific goals for the following week.

##### Fidelity

The MITI coding system will be used to assess fidelity to MI [70]. The MITI produces a behaviour count of MI-adherent and non-adherent behaviours along with a series of global ratings of dimensions of the interviewers' interactions with the parents that are characteristic of MI (evocation, collaboration, autonomy/support, direction and empathy). All participant sessions will be recorded and coded using the MITI. The MITI will also be applied to a random selection of sessions from the Usual care group to assess the health advisor's style of engagement with parents (global ratings) and the frequency of MI-adherent and non-adherent strategies.

#### Outcome measurements

All measures will be collected at baseline, 12 and 24 months as outlined below. Height, weight, waist circumference and body composition (Tanita BC-418) will be measured as described for screening.

Physical activity will be assessed over seven days using Actigraph accelerometers (GTX3) [72,73]. Parents will be asked to record the time their child got up and went to bed on a daily log. The accelerometers will be worn 24 hours a day (except swimming or bathing) and are attached to belts and placed at the waist in line with the right knee. Measures of sedentary time (television viewing and computer use) will be obtained by questionnaire.

Dietary intake will be assessed using the Children's Dietary Questionnaire [74], which assesses intake patterns over the past week for which intake is recommended (fruit, vegetables, water, reduced fat products) and foods for which intake is discouraged (high fat/sugar foods/non-core foods, sweetened beverages and full fat dairy products). The questionnaire has demonstrated acceptable reliability and relative validity at the group level, for children of this age [74]. Portion size of vegetables, meat and starch-based foods will be assessed by three brief questions which have been validated by duplicate 24-hour recall measures in 7-year old children ([name], unpublished manuscript). Food availability in the home will be assessed using a modified version of the Home Food Inventory [75]. This questionnaire assesses whether a multitude of foods and beverages are present in the home on a specific occasion and creates an obesogenic household food availability score.

The Lifestyle Behaviour Checklist will be used to assess what challenges parents of overweight children face in managing their children's behaviour and how we might address this as part of the tailored package treatment [76]. The Checklist includes 26 weight-related behaviours and asks parents to rate how much of a problem each is, and their confidence in changing each behaviour. Child behaviour will be assessed using the Strengths and Difficulties questionnaire [77].

Quality of life (QoL) will be assessed using the Pediatric Quality of Life Inventory (PedsQL4.0), a validated 23-item questionnaire for children aged 2 to 18 years which assesses physical, emotional, social and school functioning [78]. Decreases in physical and social functioning have been observed in obese compared with normal weight children [79] and are not restricted to the severely obese [80], although community samples often report higher QoL than clinical obese samples [79,81]. Parent-proxy versions of the questionnaire will be used as appropriate (Toddler if 4 years, Young Child if 5-7 years and Child if 8 years) and provide a reliable and valid measure of QoL in children [82]. Furthermore, a recent large representative Australian study [79] demonstrated that children's subjective response to their overweight was very comparable to that of their parents. As utilities have not been determined for PedsQL, quality of life will also be measured using the Health Utilities Index [83,84]. The 40-item version (HUI23P4E.40Q) based on the complementary HUI Mark 2 (seven attributes) and Mark 3 (eight attributes) questionnaires will be answered by a parent/guardian on behalf of each child.

#### Power calculations and statistics

Previous work from our group measured height and weight in more than 1000 children aged 2-18 years and asked parents whether they would be interested in attending a lifestyle programme if one was offered; 45% of parents of overweight children expressed interest ([name], unpublished). Thus we wanted to screen enough children to detect a difference in the proportion agreeing to participate in the intervention of 15%, assuming 45% for the Usual care and 60% for the MI feedback condition. It was estimated that 186 children would be required in each group to give 80% power at the 5% level of significance to detect such a difference.

Sample size estimations for the intervention were based on the literature and have been provided for the main outcome variable (BMI z-score [85]) and secondary outcome variables where appropriate (physical activity [86], quality of life [79] and dietary intake [74]). Our study has 90% power at the 5% level of significance to detect differences of i) 0.20 units of BMI z-score with 99 children in each intervention group, ii) 100 counts/minute (14% difference in physical activity) with 35 children in each group and a difference of 20 minutes/day of MVPA with 71 children in each group, and iii) 6 points on the quality of life scale (minimal clinically significant difference is 4.5 points [78]) with 51 children in each group, and iv) a difference in non-core foods diet score of 0.5 with 78 children in each group. Thus a sufficient sample size for all 5 measures would involve approximately 100 children per group. However, allowing for a 20% drop-out increases the numbers required to 125 children per group. Thus all 400 children given feedback will be invited into the intervention to recruit a minimum of 250 (125 per group) into the intervention. A mixed model, adjusting for the baseline measure will be used to analyse the data. The model will test for differences between treatments at the two time periods and the analysis will conform to the CONSORT statement for analysing randomised control trials [87].

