This approach misses a prime opportunity to intervene in a positive manner at an age where behaviour change may be more achievable. Before this can occur however, we need to find the best way of informing parents of young children that their child is overweight so that 1) they are able to accept and understand the information and the associated risks of their child's weight status, and 2) their motivation and ability to make the behavioural changes required is maximised [12]. Despite increasing use of routine screening for overweight worldwide, little research has examined how parents react to receiving this information. Parents of overweight preschool-aged children who received information regarding their child's weight status in the form of a report card detailing whether their child was normal weight, at risk of overweight or overweight [13] were far more likely (P < 0.001) to be upset about the feedback than parents of overweight children who received a report card detailing height and weight only [14]. Furthermore, half of the parents in the former group rejected the classification of their child as being overweight, saying it did not change their perception of the child's weight and only 24% of parents with overweight children and 6% of those with children classified as at risk of overweight felt that action regarding their child's weight was required [14]. In contrast, a Canadian study in preschoolers [15] showed that 85% of parents of overweight children were happy with the information provided during the measurement process, although it was unclear what feedback was given apart from plotting the child's weight-for-height. Work in school-aged children demonstrates that the majority of parents want to know the weight status of their child [16,17] even though large proportions of children (both normal weight and overweight) may feel uncomfortable discussing the results with their parents [16].

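### The Phase 2 target of 250 from 400 invited families needs 62.5% uptake, but the protocol's own 45%/60% assumption gives about 210, which puts power for BMI z-score near 85% rather than 90%

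*Protocol article*

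**What the plan says.** All the figures are in the protocol article, Methods/Design, under Power calculations and statistics.

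- **Phase 1.** The comparison of feedback methods is meant to "detect a difference in the proportion agreeing to participate in the intervention of 15" percent, "assuming 45% for the Usual care and 60% for the MI feedback condition". The lower rate comes from the group's previous survey, in which "45% of parents of overweight children expressed interest". The resulting size is that "186 children would be required in each group to give 80% power at the 5% level of significance".
- **Phase 2.** The section states "Our study has 90% power at the 5% level of significance to detect differences of" several sizes. For the main outcome this is "0.20 units of BMI z-score with 99 children in each intervention group". The secondary outcomes need 35 (activity counts), 71 (MVPA), 51 (quality of life) and 78 (non-core foods score) per group. The requirement is rounded to about 100 per group and raised to 125 for 20% drop-out.
- **Link between the phases.** "Thus all 400 children given feedback will be invited into the intervention to recruit a minimum of 250 (125 per group) into the intervention".

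Under Phase 2: Treatment, families are invited after the follow-up feedback interview, and only those who consent are randomised. The Phase 1 endpoint (agreeing to take part) and the Phase 2 recruitment rate are therefore the same event in the same families.

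**The concern.** One section uses two incompatible values for one quantity. Phase 1 expects 45% and 60% of families to agree. Phase 2 relies on 62.5% of the same families agreeing, and presents inviting all 400 as the way to get there. If Phase 1 goes exactly as assumed, Phase 2 falls short of its stated minimum.

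What is at stake is the 90% power claimed for BMI z-score. Of the five measures sized in the section, it has the largest requirement and so is the one exposed to a shortfall.

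**Working it through.** **Inputs, all from Power calculations and statistics:** uptake 45% and 60%; 400 invited; minimum 250 enrolled; 99 per group for 0.20 BMI z-score at 90% power and 5% significance; 20% drop-out. **Assumed:** two-sided tests, and feedback allocated 1:1 (200/200), in line with the equal Phase 1 group sizes.

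**1. The protocol's own figures reproduce.**
- Phase 1: the two-proportion formula for 0.45 v 0.60 at 80% power gives 173 per group, or 186 with continuity correction, as stated.
- Phase 2: 100 / (1 − 0.20) = 125 per group, 250 in total, as stated.

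**2. Uptake needed against uptake assumed.**
- Needed: 250 / 400 = 62.5%.
- Assumed: 200 × 0.45 + 200 × 0.60 = 90 + 120 = 210, which is 52.5%.
- At 60% in both arms: 400 × 0.60 = 240, still below 250.
- With Usual care feedback at 45%, the MI arm would need (250 − 90) / 200 = 80%. With MI at 60%, the Usual care arm would need (250 − 120) / 200 = 65%, which reverses the Phase 1 hypothesis.
- Under the stated rates the number enrolled has mean 210 and SD √(200 × 0.45 × 0.55 + 200 × 0.60 × 0.40) = 9.9. The exact probability of 250 or more is about 0.00003, so chance variation does not close the gap.

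**3. Power for the main outcome.** 210 entrants give 105 per group, and 105 × 0.80 = 84 remain. The SD is not stated, but it cancels: 99 per group at 90% power fixes the standardised distance at 1.960 + 1.282 = 3.242, and this scales with the square root of n.
- Power at 84 = Φ(3.242 × √(84/99) − 1.960) = Φ(1.026) ≈ 0.848. Using the t distribution with the implied SD of 0.434 gives 0.843.
- Difference detectable at 90% power = 0.20 × √(99/84) = 0.217.

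**4. Secondary outcomes at 84 per group, by the same scaling.**

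| Outcome | Needed per group | Power at 84 |
|---|---|---|
| Activity counts | 35 | over 99% |
| Quality of life | 51 | 99% |
| MVPA | 71 | 94% |
| Non-core foods score | 78 | 92% |

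**5. Sensitivity case (not the protocol's assumption): 45% in both arms.** 400 × 0.45 = 180 entrants, 90 per group, 72 after drop-out. Power for 0.20 = Φ(3.242 × √(72/99) − 1.960) ≈ 0.79.

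**6. Feedback numbers that would support 250.** 250 / 0.525 = 476.2, so about 477 families.

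**The case against.** **The power statement is conditional, and 250 is a goal rather than a forecast.** This is fair as far as it goes. The 90% is correct for 99 per group, and 125 per group is the correct inflation. What fails is the step that derives 250 from 400 invitations.

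**400 may not be a ceiling.** Under Subjects, screening continues to about 1,500 children, and the Background says that almost one in three New Zealand youngsters carry excess weight. If one third applied to these 4-8-year-olds (an assumption), about 500 would be eligible, and 500 × 0.525 ≈ 262 would meet the goal. Break-even is 477 / 1,500, about 32%. But the power section itself plans on 400, so this offers a way out without reconciling the text.

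**The loss may be smaller than 5 points.** The mixed model uses both follow-up times, so a family lost after 12 months can still contribute. With drop-out of at most 1 − 99/105 = 5.7%, 105 per group would still give 90%. Both points are true, but the protocol plans on 20%. It also does not say whether the 99 already reflects the baseline-adjusted model, so no gain can be credited.

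**A reader might infer that the 45% is itself too high.** It is expressed interest among parents of children aged 2-18, and the Background reports a study in which "only 24% of parents with overweight children and 6% of those with children classified as at risk of overweight felt that action" was required. The documents do not support that inference. Feeling that action is needed after a report card is a different endpoint from agreeing to join a programme after a face-to-face interview, and the survey behind the 45% is unpublished. The direction of any bias is speculative, and the inconsistency does not depend on it.

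**Conclusion.** The section is inconsistent as written, and no other part of the article resolves it. On its own uptake and drop-out figures, about 210 families enrol and 84 per group remain. Power for 0.20 BMI z-score is about 85%, so the type II error is about 15% instead of 10%.

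Severity is moderate. The shortfall is about 5 points on the main outcome, and 85% is still above the 80% that the same section accepts for Phase 1. A reader might infer that Phase 2 is underpowered throughout or that its comparison is compromised. Neither follows: the secondary outcomes keep at least 90% at 84 per group, and randomisation and the analysis are untouched.

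The result rests on two-sided tests, 1:1 feedback allocation, 400 families invited, and drop-outs contributing no information. It does not depend on the unstated SD.

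**What to change.** In Power calculations and statistics:

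1. State that the 45%/60% assumption yields about 210 entrants from 400 invited (105 per group, 84 after 20% drop-out).
2. Restate Phase 2 power for the main outcome as about 85% for 0.20 BMI z-score, or 90% for about 0.22.
3. Add 45% uptake in both arms as a sensitivity case: 180 entrants, 72 per group after drop-out, about 79% power. This is useful because the effect of MI on uptake is what Phase 1 is testing.
4. If 250 stays as the recruitment goal, say that it requires 62.5% uptake of 400, or about 477 families given feedback at 52.5% uptake. The goal need not be lowered.

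Items 1 to 3, and the statement in item 4, change wording only, add no participants, and make the claimed power slightly less favourable. Choosing to give feedback to about 477 families would be a real cost: at the planned yield of 400 per 1,500 screened, it means screening about 476.2 × 1,500 / 400 ≈ 1,786 children.

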### Phase 2: Treatment

When the follow-up feedback interview is complete, parents will be invited into the treatment phase. Those consenting to participate will be given additional baseline questionnaires as described below. Participants will then be randomised (stratified by feedback condition) to one of two intervention conditions; Usual care versus Tailored package.

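### Phase 2 randomisation is stratified by feedback condition, but the stated model names only the baseline measure as an adjustment (minor; the estimate stays unbiased)

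*Protocol article*

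**What the plan says.** On allocation, the protocol article (Phase 2: Treatment) states: "Participants will then be randomised (stratified by feedback condition) to one of two intervention conditions; Usual care versus Tailored package". Feedback condition is the only stratification factor named.

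On analysis, the section Power calculations and statistics states: "A mixed model, adjusting for the baseline measure will be used to analyse the data". It continues: "The model will test for differences between treatments at the two time periods". It adds that the analysis will follow CONSORT. Treatment, time and the baseline value of the outcome are therefore the terms that can be read from the text. Feedback condition is not listed as a covariate there or elsewhere.

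The same section sizes Phase 2 on BMI z-score, the main outcome: 90% power at the 5% level for "0.20 units of BMI z-score with 99 children in each intervention group". The Phase 1 sample size rests on participation rates, "assuming 45% for the Usual care and 60% for the MI feedback condition", which also fix the expected make-up of the Phase 2 population.

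**The concern.** Stratifying on a factor forces it to be balanced between the arms. That balance reduces the true sampling variance of the treatment difference if the factor is related to outcome. A model without the factor leaves its variance in the residual, so the reported standard error is larger than the true one. Confidence intervals are then a little wide and the test a little conservative.

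The factor could plausibly matter. Feedback condition is itself a randomised exposure, meant to raise parents' motivation for change, and the Tailored package is also meant to work through motivation. On the plan's own rates both strata are large. At stake is some precision in the Phase 2 comparison, and agreement between how children are allocated and how their data are analysed.

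**Working it through.** **Inputs from the protocol article.** Difference 0.20 BMI z-score units; 99 children per group; 90% power; 5% level; participation 45% after Usual care feedback and 60% after MI feedback; 400 children given feedback.

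**Assumptions.** Two-sided test; equal split of the 400 between feedback conditions; one comparison at one time point; an SD that already allows for the baseline measure and includes any feedback variance. The feedback effects tried (0 to 0.3 units) are also assumptions.

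**Step 1: the plan's figure.** n per group = 2(z₀.₉₇₅ + z₀.₉₀)² SD² / 0.20². No SD is given, so 99 cannot be verified independently. Solving for the SD gives 0.20 / (1.960 + 1.282) × √(99/2) = 0.434. For comparison, SD 0.40 needs 85 per group and SD 0.45 needs 107.

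**Step 2: stratum mix.** 200 × 0.60 = 120 and 200 × 0.45 = 90, so p = 120/210 = 0.571 of entrants have had MI feedback.

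**Step 3: variance due to feedback.** A shift of b units contributes p(1 − p)b². For b = 0.2 this is 0.2449 × 0.04 = 0.0098, which is 5.2% of 0.434² = 0.188. The residual SD with the term in the model is √(0.1884 − 0.0098) = 0.423.

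**Step 4: error rate without the term.** The model uses 0.434, while the stratified design has a true SD of 0.423. The true two-sided type I error is 2[1 − Φ(1.960 × 0.434/0.423)] = 4.4%.

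**Step 5: power at 99 per group.** With 0.20/√(2/99) = 1.407, power without the term is Φ[(1.407 − 1.960 × 0.434)/0.423] = 90.6%. With the term it is Φ(1.407/0.423 − 1.960) = 91.5%.

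| Feedback shift b | Share of variance | Residual SD with term | n per group with term | Power with term | Power without | Type I error without |
|---|---|---|---|---|---|---|
| 0 | 0% | 0.434 | 99 | 90.0% | 90.0% | 5.0% |
| 0.1 | 1.3% | 0.431 | 98 | 90.4% | 90.1% | 4.9% |
| 0.2 | 5.2% | 0.423 | 94 | 91.5% | 90.6% | 4.4% |
| 0.3 | 11.7% | 0.408 | 88 | 93.2% | 91.4% | 3.7% |

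Before rounding, the power loss at b = 0.1 is 90.37 − 90.15 = 0.2 points, and at b = 0.2 it is 91.45 − 90.59 = 0.9 points.

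**Step 6: simulation.** There were 20,000 runs of 200 children (114 and 86 per stratum, allocation exactly balanced within each). At b = 0.2, type I error was 4.4% without the term and 5.0% with it; power was 90.5% and 91.4%. At b = 0.1, power was 90.4% without and 90.7% with, a loss of 0.3 points. Type I error at b = 0.1 was 5.1% without and 5.2% with. Both lie within about 1.5 Monte Carlo standard errors (0.15 points each) of the expected values, so a shift that small is barely visible. With no feedback effect the two models agree.

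**The case against.** The strongest objection is that the article does not say the baseline measure is the sole covariate. Its account of the analysis is two sentences long, and a full covariate list is something a journal article commonly leaves to an analysis plan that is not shown. This stands as a limit on the claim: nobody can say from this document that feedback condition will be left out. But the article does more than stay silent. It names an adjustment, and what it names does not include the one factor it stratifies on.

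Second, the effect is very small and conservative. This also stands. A shift of 0.2 units would mean that one feedback interview moves BMI z-score as much as the whole two-year package is powered to detect, so the upper rows of the table are generous. In addition, activity, diet and quality-of-life baselines are collected after feedback. Adjusting for them already absorbs whatever feedback effect is present by then.

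Three stronger readings are tempting, and the documents do not support them:

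- **Confounding by feedback.** A reader might infer that, because about 57% of the Phase 2 Usual care arm will have had MI feedback, the comparison is confounded. It is not: stratification puts the same expected share in both arms, and the contrast is a valid average over feedback conditions. The article states no aim of testing whether the package effect depends on feedback.
- **Age and sex.** A reader might infer that these are wrongly omitted too. They are not stratification factors, and BMI z-score is by construction relative to age and sex, so their absence is no error for the main outcome. Any precision gain for the secondary outcomes would rest on figures the document does not give.
- **Too many false positives.** The type I error falls below 5%; it does not rise above it.

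**Conclusion.** The point holds as a minor mismatch between design and stated analysis. Followed literally, the model gives an unbiased treatment estimate with a standard error slightly too large if feedback affects outcome. For a feedback effect of 0.1 to 0.2 BMI z-score units, type I error is about 4.9% to 4.4%, and about 0.2 to 0.9 power points are lost by formula (0.3 to 0.9 by simulation). With no feedback effect there is no loss.

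These sizes rest on the back-solved SD of 0.434, the 57% mix implied by the plan's participation rates, and assumed feedback effects. The mismatch itself rests only on the two quoted statements and needs none of these assumptions. It does not threaten the trial's validity or its stated sample sizes.

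**What to change.** In Power calculations and statistics, extend the sentence on the mixed model so that it adjusts for feedback condition (the Phase 2 stratification factor) as well as the baseline measure. If the full analysis plan already lists feedback condition as a fixed effect, it is enough to bring the article's wording into line.

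The cost is one phrase and about one degree of freedom, with about 200 children expected in the analysis. No new data are needed, since feedback condition is known for every child randomised, and the required sample size does not rise in any scenario above. The term should be fixed before outcome data are seen by arm. An estimate of how the package effect varies by feedback condition would be an optional extra and is not part of this correction.
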